#### Inclusion criteria

Women aged 18–70 years old who were diagnosed with breast cancerAny stages of breast cancer patients who will start or are currently receiving different chemotherapy regimensBreast cancer patients at KCMH during the study period

#### Exclusion criteria

Women who have contraindications for chemotherapy, such as anaphylaxisWomen who have serious chemotherapy complications such as anaphylactic shock, bone marrow suppression, liver failure, acute kidney injury, and cardiac arrestWomen who are scheduled for elective surgery or other procedures requiring general anesthesia during the studyWomen who are pregnant or lactating and who are planning for pregnancy during the studyWomen who are terminally ill or inappropriate for placebo medicationWomen with any other significant disease or disorder which, in the opinion of the investigator, may have put the patient at risk because of participation in the study, or may have influenced the result of the study, or the patient’s ability to participate in the studyWomen with a known history of substance abuseWomen with a history of cannabis ingredients allergy or suspected of having an adverse reaction to cannabisWomen using antibiotics within the past 3 months or using NSAID drugsWomen consuming probiotic or prebiotic supplements

### Trial design and follow-up

#### Trial site

The prospective randomized placebo-controlled study will recruit the participants at the KCMH in Bangkok, Thailand in 2024.

#### Patient data confidentiality

Only the patients providing written informed consent will proceed to participate in the trial. All the data will be maintained confidentially by the research team.

#### Patient enrollment and recruitment

Patient demographic information will be reviewed by physicians using KCMH’s database. Online (e.g., on Facebook) and onsite poster (e.g., at KCMH) will be used to advertise the study. Patients will be recruited using the inclusion and exclusion criteria. The medical record database will be used to collect clinical and laboratory investigation data related to hormonal breast cancer subtypes, baseline symptoms, current medication including chemotherapy regime and other herbal use, emetic condition, history of surgery, history of other cancers, and history of radiotherapy.

For the recruitment, we will give the trial information to potential participants using surgeons and nurses in each surgical ward or outpatient clinic and a participant information sheet to confirm the participant’s understanding of the trial objective, procedure, benefits, and risks. If potential participants are willing to participate in the trial, they will be asked to sign an informed consent form with the understanding that they can quit the test at any time without any consequence.

#### Patient allocation and blinding

The recruited patients will be randomly allocated into 3 groups: Ganja Oil (THC 1.701 mg/mL or 0.068 mg/drop; CBD 0.003 mg/mL or 0.0001 mg/drop; CBN 0.170 mg/mL or 0.007 mg/drop; COA Ganja Oil TRCM65/05232), Metta Osot (THC 77.622 mg/mL or 3.105 mg/drop; CBD 6.737 mg/mL or 0.2695 mg/drop; CBN 7.406 mg/mL or 0.296 mg/drop; COA Metta Osot TRCM64/33,743 Rev.1), and placebo oil (THC 0 mg/mL or 0 mg/drop; CBD 0 mg/mL or 0 mg/drop; CBN 0 mg/mL or 0 mg/drop; COA Placebo TRCM64/33,742) groups. The allocation will be conducted with a 1:1:1 ratio using block randomization with a block of six by the table of random numbers for creating randomization ID. The research team will provide the randomization code in an opaque envelope to conceal allocation, mask clinicians, data collectors, and patients. Following the cannabis practice patterns of the preliminary study [29], all the participants will be received cannabis or placebo oil once per day before bedtime for 12 weeks.

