**Methods:**

A randomized, double-blinded, placebo-controlled trial will be conducted on the breast cancer cases who were diagnosed with breast cancer and currently receiving chemotherapy at King Chulalongkorn Memorial Hospital (KCMH), Bangkok, Thailand. Block randomization will be used to allocate the patients into three groups: Ganja Oil (THC 2 mg/ml; THC 0.08 mg/drop, and CBD 0.02 mg/drop), Metta Osot (THC 81 mg/ml; THC 3 mg/drop), and placebo oil. The Edmonton Symptom Assessment System (ESAS), Food Frequency Questionnaires (FFQ), microbiome profile, cytokines, and bacterial metabolites will be assessed before and after the interventions, along with pharmacokinetic and pharmacogenetic profile of the treatment during the intervention.

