### Summary of the study

Hence, the current randomized study aims to explore the efficacy of Thai cannabis oil products on the QoL of individuals diagnosed with breast cancer and treated with chemotherapies, along with the study of microbial alteration and diversity by cannabis and pharmacokinetic measures among those patients. We aim to determine the intensity of the pain and QoL experienced by cancer patients using the ESAS and the EQ-5D-5 L forms, respectively, to explore the microbiome profile, cytokines, and bacterial metabolites in hormone-dependent and independent breast cancer patients before and after the treatment with the cannabis oil or no cannabis, and to study the pharmacokinetics parameters and pharmacogenetics profile.

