#### Visits and follow-ups

There will be four visits for the recruited participants during the trial. At the first visit, research investigators will perform the enrollment by checking the eligibility screening, informed consent form, and allocation plan. Then, the blood, saliva, stool, and skin samples will be collected as a baseline and start the treatment as day 1. The next visits will be to assess the adverse drug reaction by a medical officer. At week 6, the blood samples will be collected for assessing the pharmacokinetic parameters. Week-12 visit will be the last visit at which all the participants will be assessed for any adverse reaction, and the blood, saliva, stool, and skin samples will be collected as post-treatment samples.

After the trial, patients will be asked to stop taking cannabis oil from any sources. They will be monitored for another month for withdrawal symptoms.

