### Primary outcome measures

The pain level of each patient will be assessed using the ESAS form at the last visit as primary outcome.

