## Conclusions

The clinical trial will provide the efficacy of Thai cannabis oils in breast cancer female patients in Thailand, mainly in alleviating chemotherapy-related side effects. Furthermore, it will obtain secondary factors such as QoL indexes, alteration of microbiome profile, bacterial metabolites, and cytokines before and after using the cannabis oil, pharmacokinetic parameters, and pharmacogenetic profiles.

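### One unstratified randomisation list covers women not yet on chemotherapy and women already on it, and the stated between-arm tests adjust for nothing: an avoidable loss of balance and precision, not a bias

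*Protocol article*

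**What the plan says.** All references are to the protocol article.

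- **Population.** The abstract's Methods describes women "diagnosed with breast cancer and currently receiving chemotherapy at King Chulalongkorn Memorial Hospital". Target population joins diagnosis and current chemotherapy with an *or*. Inclusion criteria accepts any stage, with chemotherapy either about to begin or already under way, on differing regimens. Sample size estimation calls the target population metastatic.
- **Allocation.** Patient allocation and blinding states: "The allocation will be conducted with a 1:1:1 ratio using block randomization with a block of six by the table of random numbers". It goes on to opaque envelopes. It names no stratification factor and no minimisation.
- **Facts known at entry.** Patient enrollment and recruitment collects "data related to hormonal breast cancer subtypes, baseline symptoms, current medication including chemotherapy regime" from the medical record.
- **Baseline.** Visits and follow-ups ties week 0 to the start of the oil, not to a point in the chemotherapy course: "samples will be collected as a baseline and start the treatment as day 1".
- **Primary outcome.** "The pain level of each patient will be assessed using the ESAS form at the last visit as primary outcome".
- **Aims.** Summary of the study includes "bacterial metabolites in hormone-dependent and independent breast cancer patients before and after the treatment". Conclusions describes the efficacy sought as "mainly in alleviating chemotherapy-related side effects".
- **Analysis.** Statistical analysis gives paired t-tests before and after treatment, and one-way ANOVA with Bonferroni correction or Kruskal-Wallis among the three arms. No covariate is named.

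**The concern.** In a trial mainly about relieving chemotherapy side effects, whether chemotherapy has begun at week 0 is an obvious candidate prognostic factor. A woman who has not started cannot have those side effects at baseline, and her change to week 12 includes their onset. A woman already on treatment may have them at baseline, and may have finished her course by week 12.

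Two separate things follow. First, blocks of six equalise arm totals but not the chemotherapy mix, and the stated tests do not correct for a difference in mix. At 30 per arm, and possibly 15 after loss, one arm could by chance hold noticeably more women who had not started. Second, whatever the mix between arms, a within-arm before/after change combines the oil with the course of chemotherapy. The first is a matter of allocation and analysis. The second comes from eligibility and the definition of week 0.

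**Working it through.** **Inputs from the article.** 90 women, 30 per arm, blocks of six, maximum loss 50%; earlier-study pain change 0.95 with SD 2.39 (Clinical practice in Thailand). The article's counts agree: 3 × 30 = 90, 90/6 = 15 blocks, 30 × (1 − 0.5) = 15 per arm at maximum loss.

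**Assumed.** The share p not yet on chemotherapy is not given. I use 0.5 and 0.3; 0.7 gives the same results as 0.3.

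**Step 1: chance imbalance with one list.** The number of not-yet-started women in each arm is binomial(n, p), independent across arms. The SD of the difference in share between two arms is √(2p(1 − p)/n). For p = 0.5 and n = 30 this is √(0.5/30) = 0.129. A gap of 20 points is 6 women of 30, or 3 of 15. Summing the three-arm binomial probabilities over all outcomes with (largest − smallest count) at or above that number gives:

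| n per arm | p | SD of difference | P(some two arms differ by ≥ 20 points) |
|---|---|---|---|
| 30 | 0.5 | 0.129 | 33% |
| 30 | 0.3 | 0.118 | 27% |
| 15 | 0.5 | 0.183 | 63% |
| 15 | 0.3 | 0.167 | 58% |

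The rows for 15 treat loss as unrelated to arm and chemotherapy status.

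**Step 2: separate lists by chemotherapy status.** Within a list every complete block is balanced, and the last, incomplete block can leave two arms apart by at most 2 women. The largest gap in share is therefore roughly 2/30, about 7 points. In 20,000 simulated trials of 90 women no gap reached 20 points.

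**Step 3: what a gap would do to the primary comparison.** If chemotherapy status shifted week-12 pain by 1 to 2 points (assumed; the article gives no figure), a 20-point gap would move an arm difference by 0.20 × 1 = 0.2 to 0.20 × 2 = 0.4 points. With SD 2.39, which is the SD of a one-month change and so only a stand-in, the standard error of an arm difference is 2.39 × √(2/30) = 0.62 at 30 per arm and 2.39 × √(2/15) = 0.87 at 15. The shift is smaller than ordinary sampling error, but not negligible beside 0.95.

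**Step 4: validity.** In 20,000 simulated null trials with a 2-point prognostic factor left out of the ANOVA (p = 0.5, SD 2.39), the type I error was 0.046 against a nominal 0.05.

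**Step 5: precision.** Taking 2.39² = 5.71 as the residual variance and p = 0.5, ignoring the factor adds 0.25 × 1² = 0.25 (4%) to 0.25 × 2² = 1.00 (18%) to the variance.

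**Step 6: hormone subtype.** If 20% were hormone-independent (assumed), 0.20 × 90 = 18 women, 6 per arm with perfect balance and 3 after 50% loss. Simulation gives some arm 4 or fewer such women in about 58% of trials with one list, about 24% when stratified on subtype alone, and about 30% with four lists by chemotherapy status and subtype.

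**The case against.** Blocked 1:1:1 randomisation without strata is a legitimate design. It balances every factor in expectation, the test already allows for chance imbalance (Step 4), and Step 3 shows a shift below the standard error. Covariates are often left to the analysis plan, which is not shown. All of this stands, and it limits the point to precision and interpretability. It does not remove it. Allocation has to be fixed before recruitment, the article spells the scheme out, and the tests it does state are unadjusted.

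A reader might infer more than the documents support:

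- *That an imbalance would pass as an oil effect, so the trial is biased.* Step 4 does not bear this out; only the single realised comparison can be shifted.
- *That the two groups move in opposite directions.* No figure shows this for pain, cytokines or microbiome. The primary outcome is also the week-12 level, not a change from week 0.
- *That stratifying would give baseline one meaning.* It evens out the mix between arms. The mixed baseline, and the paired tests that rest on it, stay as they are.
- *That allocation is what defeats the subtype aim.* Step 6 shows that numbers are the main limit, even under perfect balance.

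Stratifying at entry also does not guarantee balance among completers, which is a reason to adjust as well. Finally, if the abstract's narrower population governed, the chemotherapy contrast would shrink to differences in cycle and regimen.

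**Conclusion.** The point holds as a worthwhile improvement to design and analysis, not as an error that invalidates the trial. With one list, the chance of a gap of 20 points or more in chemotherapy status between some two arms is about 27% to 33% at 30 per arm and about 58% to 63% at 15. With separate lists it is essentially nil at entry. These figures assume that 30% to 70% of entrants have not started chemotherapy. The effect on the pain comparison (0.2 to 0.4 points for a 20-point gap, and 4% to 18% extra variance) assumes that status shifts pain by 1 to 2 points, which the article neither supports nor excludes. Before/after changes within an arm cannot be read as oil effects under any allocation scheme while both groups are eligible.

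**What to change.** 1. Reconcile the descriptions of the population in the abstract's Methods, Target population, Inclusion criteria and Sample size estimation.
2. If both groups remain eligible, prepare separate block-of-six lists by chemotherapy status at week 0 (not started / ongoing).
3. Compare week-12 ESAS pain between arms with a model that adjusts for chemotherapy status and baseline ESAS pain.
4. Hormone subtype may be a further adjustment factor or a second stratum (four lists), but state that this will not make the subtype aim well powered.
5. Record cycle number and planned last cycle date at the week-0 visit (T1). Define any subgroup by that planned date. Whether chemotherapy was actually still running at week 12 is a post-randomisation event and should not define one.
6. Draw conclusions about the oils from between-arm comparisons, and present the paired before/after results as descriptive.

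**Cost.** Two envelope lists (four if subtype is added) in place of one, prepared before recruitment, and two extra items on the week-0 form. No extra patients, visits or samples. Each list may end in an incomplete block, so with two lists any two arm totals may differ by up to 2 × 2 = 4 women.

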#### Trial timepoints

Assessment of adverse drug effects will be collected with 4 time points: 0th, 1st, 6th, 12nd weeks of the trial day. The pain symptoms, QoL and diet pattern will be recorded with 3 time points: 0th, 6th, 12nd weeks. The blood collection (3 mL) for pharmacokinetic and pharmacogenetic tests will be performed on 2 time points: 0th, 6th weeks. The blood (10 mL), feces, skin scrapping, and saliva samples will be taken for biochemistry tests (plasma/ serum), microbiome (gut/ skin/ saliva), cytokines (plasma) and bacterial metabolites (serum/ feces) will be analyzed at 2 time points: 0th, 12nd weeks. The overview of the tests and visits of the clinical trial was shown on the following Table 1.

**Table 1 Tab1:** SPIRIT schedule of enrolment and assessments

#	Timepoint	Week-0 baseline	Week-1 follow-up	Week-6 follow-up	Week-12 follow-up
		T1	T2	T3	T4
1	**Enrolment**				
	Eligibility screening	x			
	Informed consent	x			
	Allocation	x			
2	**Assessment**				
	CRF01 Case Record Form^a^	x			
	CRF02 FW & ADR^b^	x	x	x	x
	CRF03 ESAS	x		x	x
	CRF04 EQ-5D-5 L	x		x	x
	CRF05 Food Frequency Questionnaire	x		x	x
3	**Blood Samples, Serum**				
	Blood Chemistry^c^	x			x
	Cytokines^d^	x			x
	Bacterial Metabolites^e^	x			x
	Pharmacokinetics parameters	x		x	
	Pharmacogenetics parameters	x		x	
4	**Feces Samples**				
	Fecal Microbiome Profile	x			x
	Fecal Bile Acid Profile^f^	x			x
	Fecal SCFAs^g^ and BCFAs^h^	x			x
5	**Skin Samples**				
	Skin Microbiome Profile	x			x
6	**Saliva Samples**				
	Oral Microbiome Profile	x			x

^a^Demographic and Epidemiological Factors: age, weight, height, waist circumference, hip circumference, neck circumference, alcohol consumption, smoking status, occupation, monthly income, method of health payment, and highest education

^b^Follow up and adverse drug reaction: vital signs, physical examination, lab results to assess liver, kidney and heart function, pharmacokinetic record form, drug tolerance assessment form, and adverse event assessment form

^c^Blood Chemistry: lipid profile, liver function test (LFT)

^d^Cytokines: interleukin-17, interferon-gamma, Interleukin-10, tumor growth factor-beta

^e^Bacterial Metabolites: lipopolysaccharide binding protein, sCD14 levels, equol, cadaverine

^f^Fecal Bile Acid Profile: chenodeoxycholic acid, deoxycholic acid, lithocholic acid

^g^SCFAs: butyric acid, propionic acid, acetic acid

^h^BCFAs: iso-butyric acid

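### A single disclosed block of six at one hospital weakens concealment if Metta Osot patients can be recognised, and the envelope named as the masking device can only conceal allocation

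*Protocol article*

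**What the plan says.** The abstract describes the design: "A randomized, double-blinded, placebo-controlled trial will be conducted". Patient allocation and blinding gives the sequence ("The allocation will be conducted with a 1:1:1 ratio using block randomization with a block of six by the table of random numbers") and then one device for both concealment and masking: "The research team will provide the randomization code in an opaque envelope to conceal allocation, mask clinicians, data collectors, and patients".

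The same section gives the certificate-of-analysis contents of the three oils: "Ganja Oil (THC 1.701 mg/mL or 0.068 mg/drop"; "Metta Osot (THC 77.622 mg/mL or 3.105 mg/drop"; "placebo oil (THC 0 mg/mL or 0 mg/drop". All arms take their oil once daily at bedtime for 12 weeks.

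Recruitment is at one hospital (Trial site). Visits and follow-ups says that at the first visit "research investigators will perform the enrollment by checking the eligibility screening, informed consent form, and allocation plan". Adverse reactions are assessed at weeks 0, 1, 6 and 12, and ESAS at weeks 0, 6 and 12. Footnote b of Table 1 lists, within the follow-up and adverse-reaction form CRF02, a "pharmacokinetic record form, drug tolerance assessment form, and adverse event assessment form". The primary outcome is ESAS pain at the last visit.

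**The concern.** Concealment and masking are different safeguards. Concealment ends when the patient is assigned; masking has to last until the week-12 ESAS. The article assigns both to an envelope, which protects nothing once it is opened.

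The two safeguards fail in different ways.

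- **Selection at enrolment.** With one block size printed in the protocol and one enrolment sequence, staff who infer the arms of earlier patients can work out some of the later ones. The exclusion criteria leave room to act on that: they rest partly on investigator opinion and on whether a woman is suitable for placebo.
- **Functional unblinding.** A patient who feels the effect of a high-THC oil may rate her pain according to what she expects of it. This would happen with any block size.

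At stake are the comparability of the arms at baseline and the interpretation of a self-rated primary outcome.

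**Working it through.** **THC contents.** The stated per-drop figures come first. The article's own pairs imply 3.105/77.622 = 0.040 mL per drop. At that volume 77.622 × 0.04 = 3.105 mg and 1.701 × 0.04 = 0.068 mg, both as stated. The ratios of Metta Osot to Ganja Oil are:

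- certificate figures: 3.105/0.068 = 45.7 per drop; 77.622/1.701 = 45.6 per mL;
- nominal figures in the abstract: 3/0.08 = 37.5 per drop; 81/2 = 40.5 per mL.

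These are ratios per drop, not per dose. The allocation section does not state drops per dose; it refers to the practice patterns of the earlier cohort.

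**Predictability of a block of six.** Inputs: 1:1:1, so two of each arm per block, with 90 equally likely orderings; 90 patients, so 15 blocks.

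*All earlier arms in the block known.* The guess is always the arm with most places left. The next allocation is certain when all remaining places belong to one arm. At position 5 the last two places are the same arm with probability 3 × 1/15 = 20%; position 6 is always certain.

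*Only Metta Osot recognisable.* The two Metta Osot places form one of 15 equally likely pairs. Position k is certainly not Metta Osot if both fell among the first k − 1 places, with probability C(k−1, 2)/15. It is certainly Metta Osot if every remaining place is Metta Osot: 1/15 at position 5 and 5/15 at position 6.

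| Position | Correct guess, all known | Certain, all known | Certainly not Metta Osot | Certainly Metta Osot |
|---|---|---|---|---|
| 1 | 33.3% | 0 | 0 | 0 |
| 2 | 40.0% | 0 | 0 | 0 |
| 3 | 50.0% | 0 | 1/15 | 0 |
| 4 | 53.3% | 0 | 3/15 | 0 |
| 5 | 60.0% | 20% | 6/15 | 1/15 |
| 6 | 100% | 100% | 10/15 | 5/15 |
| Mean | 56.1% | 20.0% | 22.2% | 6.7% |

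- All earlier arms known: 20% of allocations (18 of 90) are certain. Guesses are right 56% of the time, against 33% by chance.
- Only Metta Osot recognised: 22.2% + 6.7% = 28.9% (26 of 90) are certain as to Metta Osot or not. Of these, 20 are certainly not Metta Osot and 6 certainly are. Guesses of Metta Osot or not are right 74% of the time, against 67% by chance.
- No earlier arm known: guesses are right 33% of the time, so the block size gives no advantage.

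**Varied blocks.** In 3,000 simulated sequences of 90 patients, a guesser who knows all earlier arms and picks the least-used one is right 55% of the time with random blocks of 3, 6 and 9, and 52% with 6, 9 and 12, against 56% with the fixed six. Average accuracy barely moves. The gain is that block ends are hidden, so the last place in a block is no longer known for certain.

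**Functional unblinding, illustration only.** The article gives no figure for reporting bias, so a range is assumed. The SD of 2.39 is that of the ESAS pain change in the earlier cohort, quoted in the Introduction. With a two-sided 5% normal test, SE = 2.39 × √(2/n) and no true effect, a pure reporting shift b in one arm gives a false-positive rate of Φ(b/SE − 1.96) + Φ(−b/SE − 1.96):

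| Assumed shift (ESAS points) | 30 per arm | 15 per arm (after the planned maximum 50% loss) |
|---|---|---|
| 0.5 | 13% | 9% |
| 1.0 | 37% | 21% |
| 1.5 | 68% | 40% |

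**The case against.** A reader might infer that the blind rests on nothing but the envelope and the block size, so that allocations are guessable and the pain result is biased. The documents do not support that. The trial is stated to be double-blind, with a placebo oil on the same bedtime schedule. The random numbers create a randomization ID and the envelope holds a code, which is compatible with coded product. The article does not say that an arm name reaches enrolling or assessing staff. Product matching and code custody are details that a condensed article may leave to the full protocol, so their absence is no finding. Block size belongs to sequence generation and concealment, not to the blind.

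The predictability figures are also conditional. The 20% requires telling Ganja Oil (0.068 mg per drop) from placebo (0), and nothing suggests that staff could. The 29% is mostly knowledge that the next patient will not get Metta Osot. Recognition at week 1 helps only if earlier block members reach that visit before the next enrolment, and no recruitment rate is given. Nothing shows that Metta Osot at bedtime is recognisable; the abstract reports that doses in a pilot study were generally well tolerated.

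A reader might likewise infer that CRF02 discloses the arm through week-6 drug levels. The form is completed at weeks 0, 1, 6 and 12, while pharmacokinetic blood is drawn at weeks 0 and 6. The record form could equally hold sampling or dosing times, so the leak arises only if concentrations are entered there.

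All of this stands. It leaves three things untouched: the block size is fixed and disclosed at a single site, the envelope is given a masking task it cannot perform, and the two active oils differ widely in THC.

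**Conclusion.** The point holds as a weakness in a stated method, not as proof of a broken blind. The allocation section should not fix and disclose one block size for one hospital, nor name an envelope as the means of masking for 12 weeks.

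For enrolment, the exposure ranges from none (no earlier arm known), through 20% certain (all earlier arms known), to 29% certain as to Metta Osot or not (only that arm recognised, and only 6.7% as certainly Metta Osot). These are upper bounds under the stated knowledge.

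For the primary outcome, the risk is separate and independent of block size, and it would fall mainly on the Metta Osot comparisons. Its size cannot be derived from the documents; the false-positive rates above rest on assumed shifts and a borrowed SD. The changes are worth making because they are nearly free and leave treatment untouched.

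**What to change.** 1. Replace the fixed block of six with randomly varied block sizes, for example 3, 6 and 9, and keep the sizes out of anything enrolling staff see.
2. Reword the envelope sentence: the envelope serves concealment until assignment, and masking rests on coded product.
3. Keep week-6 THC and CBD concentrations out of CRF02 and away from site staff until database lock.
4. At visits where both are done, complete ESAS before the adverse-reaction interview.

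Items 1 and 2 address concealment and the wording; items 3 and 4 limit unblinding of the pain rating. Varying the blocks does nothing about patients recognising THC effects. Asking patients and assessors to guess the arm is optional. The article names no pharmacy, so none of this should presume one.

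The cost is a new randomisation list, a data-release rule and an instruction on the order of assessments. Balance becomes slightly less exact if recruitment stops mid-block: two arms can differ by up to three patients within a block of nine, against two within a block of six. At exactly 90 patients, the fixed six would end on a complete block (90/6 = 15).
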